#### ECT

##### Equipment

ECT will be administered with a Thymatron System IV Somatics Inc. or MECTA 5000 or 4000 models, providing brief-pulse, square wave, constant current.

##### Anaesthesia

Preferably the short acting anaesthetic thiopental will be used to obtain anaesthesia. Anaesthetic dose should be kept to a minimum (1.5-2.5 mg/kg iv). A dose large enough to inhibit ciliary reflex is usually larger than needed for ECT. Excessive anaesthetic dosage may raise seizure threshold and shorten seizure duration. The appropriateness of dosage will be determined at each treatment and adjustments made at subsequent treatments. Other anaesthetics may be used if indicated. Succinylcholine in a dose of 0.5 - 1.0 mg/kg iv will be used as a muscle relaxant. All patients will be hyperoxygenated during treatment. Patients breathe oxygen enriched air 1 to 2 minutes before and during the initiation of anaesthesia. Pulse oximetry will be used. Hyperventilation should be maintained even with high oxygen saturation. Use of other medication necessary during anaesthesia (e.g. for premedication or termination of prolonged seizure) is at the decision by the anaesthesiologist.

##### Stimulation electrodes placement

Stimulation electrodes will be placed ad modem d'Elia [32] (Right unilateral electrode placement, RUL). It is well documented that high dosage ECT with unilateral placement of stimulation electrodes is as effective as bilateral placement [19,20]. If the stimulation electrodes are placed on the non-dominant side, unilateral stimulation is associated with less cognitive impairment than bilateral stimulation [19,21]. In this study electrodes will be placed over the right hemisphere.

##### Stimulus

Using ultra-brief stimulation pulses (0.5 ms or less) is more effective and associated with less cognitive impairment than longer pulses and sinus current. The duration of the stimulus pulse in our study will be 0.5 ms. In the present study the initial stimulus energy will be determined by an aged based method, where the energy (E) is calculated as following [33]: Patient's age in years × 5 ≅ stimulus charge in mC. The Thymatron delivers a charge of 25.2 to 504 mC in 20 equal steps, set by the % Energy dial. According to the above formula this makes: Patient's age in years ≅% Energy. In order to consider gender specific differences in seizure threshold the % Energy will be adapted as following: For male patients: % Energy + 5 to 10%. For female patients: % Energy - 5 to10%. If there is not obtained a sufficient seizure in one session determined by clinicians decision (based on seizure duration, δ-waves and clinical effect) the patient may be restimulated in the same session or/and stimulus parameter will be adjusted in next session. The treatment should be followed by a comatose state, from which consciousness is gradually regained [34].

##### Medication after seizure

In case of postictal delirium either midazolam (0.5 - 2.5 mg iv) or thiopental (half of anaesthetic dose) may be administered. Postictal headache may be treated with paracetamol 1000 mg or ibuprofen 400 mg (can be repeated). Metoclopramide 10 mg tablets or iv in case of nausea.

##### Duration of treatment

Three sessions per week for up to six weeks, a total of up to 18 sessions. The ECT series may be tapered off when response is achieved by gradually increasing the intervals between treatments.

##### Quality Control

The ECT instruments will be regularly tested for effects and calibrated.

##### Registration

Each ECT session will be registered with the parameters listed in table 3.

**Table 3 T3:** Parameters recorded after each ECT-session

Anaesthetic drugs used
Energy (%)
Charge delivered
Motor activity
Seizure duration
Postictal suppression index
Sustained coherence
Sustained power
Seizure energy index
Quality of δ-waves, seizure ending and postictal supression
Basal and peak heart rate
Time to reorientation (personal data, time, place)
Mood state immediate after recovery of orientation and the following hours, expressed like "good, neutral, don't know, better, changed" or "bad, depressed, no better, no change, feeling of not having had a treatment

##### Maintenance-treatment after ECT-course

At the end of course of ECT each patient will be given maintenance medication after clinicians' decision following treatment guidelines described elsewhere [31].

#### Medication in control group - Treatment as Usual

All participating hospitals use the treatment algorithm according to Goodwin and Jamison [35] adapted to Norwegian conditions as their routine treatment for bipolar depression. See Additional file 1. In addition the use of alimemazine (max dose 30 mg daily), chlorpromazine (max dose 25 mg × 2 daily), chlorprothixene (max dose 20 mg × 2), mianserine (max dose 10 mg daily) is allowed. In the control group the use of alopam 15 mg up to 3 times/day, zolpidem 10mg or zoplicone 7,5 mg is allowed as part of treatment as usual.

##### Wash out Phase

The recommended time for patients to be without concomitant medication in contradiction to the study protocol is 5 t 1/2 for patients randomized to ECT and a varying time for patients randomized to treatment as usual.

##### Randomized treatment Phase - treatment regimens

For treatment regimes see Additional file 1.

The treatment algorithm according to Goodwin and Jamison [35] is to be followed step by step. It is however possible for the clinician to depart from the stepwise use of the algorithm if they out of their knowledge to the patient consider one of the medicaments unacceptable or of no use to the patient. Patients that experience intolerable side effects on one medication listed in the algorithm may be switched to the next treatment option according to the algorithm.

##### Continuation phase

After the 6 weeks randomized treatment phase, the patients continue with medication recommended by their clinician guided by a relevant treatment algorithm as for example [31].

##### Treatment compliance

Compliance will be assessed based on patient's record of compliance (at each visit 3-10) as well as by serum level monitoring at week 3.

##### Concomitant Therapy

All medications (prescriptions or over the counter medications) continued at the start of the trial, or started during the trial and different from the trial medication must be documented. Patients, who receive ECT during the follow- up period, will be excluded from further analyses of neuropsychological functioning.

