**Discussion:**

This study is the first randomized controlled trial that aims to investigate whether electroconvulsive therapy is better than pharmacological treatment as usual in treatment resistant bipolar depression. Possible long lasting cognitive side effects will be evaluated. The study is investigator initiated, without support from industry.

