**Figure 1 F1:**
[figure not shown]
**Flow Chart of Study Design**.

Relevant patients with depression are addressed in order to establish whether they are willing to be screened for the study. The patients must be assigned a patient number and sign the consent form after receiving oral and written information about the study prior to undergoing any study procedures.

Each treatment trial lasts 6 weeks. The medication that would be used if a patient should be randomized to drug treatment will be determined at enrolment, before randomisation. If a patient receives ECT and reaches remission earlier than six weeks, the ECT treatment is terminated and the patient is switched to maintenance therapy. If a patient or the treating clinician decides that the patient could receive better treatment outside of the study, the patient may leave the study at all times, as specified in the informed consent. In case of remission after the six weeks trial the patient continues with maintenance drug treatment at the clinicians decision, guided by relevant algorithm as for example in Goodwin & Jamison 2007 [31]. In case of non- remission the clinician might consider the other treatment condition. This will not be part of the present study.

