#### Statistical analysis

Response and remission rates will be compared using Chi Square tests. Secondary outcomes and cognitive function will be analysed with multiple regression analyses and other suitable statistical methods. ANOVAs and t-test will be made on a LOCF basis. Categorical variables will be analysed using chi square tests. Ordinal variables will be analysed using non-parametric tests in addition to using T tests and ANOVA. Time to remission and/or response will be analysed using survival analysis. The statistical analysis will be done by the scientific research team with assistance from experts in statistics. All patients who receive at least one medication with study medicine or ECT will be included in the analysis of the safety, demographic and baseline characteristic data. An analysis of treatment-emergent adverse events will be performed. All subjects who receive at least one medication with study medicine and provide post - baseline efficacy measurements will be included in efficacy data analyses (intention to treat). We will use last observations carried forward for subjects who leave the study prematurely. Analyses only including patients fulfilling the treatment will also be done. Baseline for all analyses is visit 2 (start of drug or ECT treatment).

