##### Definitions

Response: at least a 50% reduction of the baseline MADRS score.

Remission: MADRS score of 12 or less at the end of trial.

New episode: A patient who has previously responded to treatment meets the DSM-IV criteria for Major Depressive Episode or Manic episode.

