## Discussion

This study protocol presents a randomized controlled trial for a population of in-patients with serious, therapy resistant bipolar depressions. We believe that this study is important and needed, and that the main results may influence daily clinical practise. Both bipolar depression and the treatments for bipolar depression are associated with cognitive impairments. This study may give important information of short-and long-time contributions and effects of these different factors.

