### Methodological weaknesses

The use and policy regarding ECT differs between countries and hospitals. Thus there are no published guidelines defining objective clinical criteria for indications of treatment with ECT in bipolar depressions. In the present protocol "indication for ECT" is one of the inclusion criteria. This means that treatment with ECT would have been probable according to hospital practice regardless of the present study.

The assessments are performed by specially trained research staff which is not blinded for grouping of the patients. Most of the patients are acutely admitted to psychiatric acute wards due to the extensive symptom pressure.

The multicentre site design has potential problems regarding assessments and inter-rater reliability. However, multicentre design is a necessity in order to include sufficient number of patients in a reasonable time span. All raters and participants in the study have taken part in mutual training-sessions in the different assessments and rating scales. All participants have taken part in interrater-scorings. The scorings for the different study centres and the different participants are satisfactory.

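### Excluding patients who receive ECT in follow-up conditions the week 26 and later cognitive comparison on a post-randomisation event related to outcome

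*Protocol article*

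**What the plan says.** The rule stands under Concomitant Therapy: "Patients, who receive ECT during the follow- up period, will be excluded from further analyses of neuropsychological functioning". It names no arm.

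The text below Figure 1 (Study design) describes what may follow the six-week phase: "In case of non- remission the clinician might consider the other treatment condition". The next sentence there places that later treatment outside the study. For patients who had ECT, the section on maintenance treatment says: "At the end of course of ECT each patient will be given maintenance medication after clinicians' decision".

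An indication for ECT is an inclusion criterion (Table 1). Methodological weaknesses explains its meaning: "This means that treatment with ECT would have been probable according to hospital practice regardless of the present study".

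Table 4 schedules neuropsychological testing at visit 1, week 6, week 26 and weeks 30-52, with no exemption for patients who change treatment. The abstract promises: "Possible long lasting cognitive side effects will be evaluated". On the analysis itself, the Statistical analysis section says only: "Secondary outcomes and cognitive function will be analysed with multiple regression analyses and other suitable statistical methods".

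**The concern.** Whether a patient receives ECT after week 6 depends on how that patient fared on the assigned treatment. Remission is defined after randomisation ("Remission: MADRS score of 12 or less at the end of trial"), and non-remission opens the way to the other condition. For a control patient that condition is ECT, and the patient is dropped. For an ECT-arm patient it is drugs, and the patient is kept. The same outcome thus leads to opposite analysis status in the two arms.

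The trigger is also related to what is measured. The article's Discussion says: "Both bipolar depression and the treatments for bipolar depression are associated with cognitive impairments". If persisting depression lowers test scores, dropping non-remitting controls leaves a control group that looks better than its arm, and ECT looks worse. Dropping ECT-arm patients who had a further course works the other way. The kept patients cannot show which effect prevails. At stake is the randomised comparison of lasting cognitive effects, a stated aim of the trial.

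**Working it through.** **The plan's own figure.** The only computed figure is the sample size for MADRS change: difference 4, SD 7, two-sided alpha 0.05, power 0.90. The exact t-test needs 65.3 per arm, so 66 per arm and 132 in total, with power 0.903. The stated 132 is reproduced, and this point does not touch it. Below, 66 per arm serves only as an illustrative size. The document gives no follow-up ECT rate, non-remission rate or cognitive gap, so all of these are assumptions.

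**Check 1: general formula.** Let f be the share of an arm that is dropped, and let dropped patients score *gap* below those kept. The arm's full mean is then the kept mean minus gap × f, so dropping raises the arm's mean by gap × f. With the same gap in both arms, the bias against ECT is

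gap × (f_control − f_ECT).

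Take 20-50% for control, 5-15% for ECT, and gaps of 0.3-0.8 SD:

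- smallest: 0.3 × (0.20 − 0.15) = 0.015 SD
- mid-range: 0.5 × (0.35 − 0.10) = 0.125 SD
- largest: 0.8 × (0.50 − 0.05) = 0.36 SD

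**Check 2: milder model.** Suppose only non-remitters cross, nobody in the ECT arm is dropped, and ECT has no true lasting effect. Let p be the non-remission rate, x the share of control non-remitters who cross, and g the deficit of non-remitters against remitters. The non-remitter share among kept controls is p(1 − x)/(1 − px), so the upward shift of the control mean is

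g × [p − p(1 − x)/(1 − px)].

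- p = 0.6, x = 0.4, g = 0.3: 66 × 0.6 × 0.4 = 15.8 controls removed. The non-remitter share falls from 60% to 0.36/0.76 = 47%. The shift is 0.3 × (0.600 − 0.474) = 0.04 SD.
- Over p = 0.4-0.7, x = 0.2-0.6 and g = 0.2-0.5: about 5 to 28 of 66 controls removed, and a shift of about 0.01 to 0.11 SD.
- Simulated type I error at p = 0.6 in both arms, for g = 0.2, 0.3 and 0.5: 0.048, 0.055 and 0.061 at x = 0.4; 0.056, 0.065 and 0.087 at x = 0.6 (6,000 trials each).
- With p = 0.6 and x = 0.4 in both arms, the bias is zero. In this model it comes wholly from unequal removal.

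**Why the two ranges differ.** The gap in Check 1 is between dropped and kept patients, and kept controls still include non-remitters. If 35% are dropped and 60% do not remit, 0.25/0.65 = 38% of kept controls are non-remitters. A dropped-versus-kept gap of 0.5 SD then requires g = 0.5/(1 − 0.385) = 0.81 SD, if remission status alone drives selection. The upper part of the Check 1 range therefore needs strong assumptions.

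**Check 3: direction.** If the gap differs by arm, the bias against ECT is gap_control × f_control − gap_ECT × f_ECT. Within the same ranges, 0.3 × 0.20 − 0.8 × 0.15 = −0.06 SD, which favours ECT. The sign is not fixed.

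**The case against.** The strongest defence is that the rule is deliberate. The protocol places treatment after a switch outside the study, and a control patient who has had ECT no longer informs a contrast of ECT with no ECT. For a harm question, counting such patients as controls can hide a lasting effect. That stands as a reason not to rely on an as-randomised analysis alone. It does not rescue deletion, because the controls who remain are selected on how they fared.

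The defence is also right that the rule concerns only further analyses, so week 6 is untouched, and that visit 10 is meant to take place in a euthymic state where possible. This softens the mood mechanism at the last visit but not at week 26.

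Three stronger readings are tempting and are not supported:

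- A reader might infer that the rule removes control patients only. Its wording is neutral between arms. Predominance in the control arm is an inference, though a strong one, from the switching provision, the entry criterion and the maintenance section.
- A reader might infer that ECT will be made to look more harmful. Check 3 shows that the opposite is possible.
- A reader might put a figure on lost power from 66 per arm. Table 1 sets extra language requirements for patients enrolled to neuropsychological assessment, so the number tested may be below 132, and no power figure for these tests can be drawn from the document.

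**Conclusion.** The concern holds for the cognitive comparison at week 26 and later, and only there. Followed as written, the rule selects patients on an event that arises after randomisation and is related to outcome, so that comparison is no longer a randomised one. Confidence is high for the mechanism and low for size and net direction, which the document cannot settle. The illustrations run from about 0.015 to 0.36 SD under the wider assumptions with a common gap, and from 0.01 to 0.11 SD under the milder ones. In the milder case, type I error stays close to nominal unless crossover and the mood-related gap are both large. A stated aim is affected while the primary endpoint is intact, so this is a cheap and worthwhile improvement, not a fault that undermines the trial.

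**What to change.** Replace the exclusion sentence under Concomitant Therapy. For cognitive outcomes at week 26 and later, report side by side:

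- (a) an analysis of all randomised patients tested, by assigned arm, whatever treatment was given in follow-up; and
- (b) a mixed model in which only scores obtained after follow-up ECT are set to missing, keeping each patient's earlier visits.

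Report the number of patients with follow-up ECT by arm.

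Part (b) is close to what the present sentence intends. What it adds is that earlier scores help to stand in for the missing ones, on the assumption that those scores and the assigned arm account for who goes on to ECT. Part (a) keeps the randomised groups.

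The cost is a change of wording and one extra model. The tests are already scheduled in Table 4, so no new visits are needed and clinical management is unchanged. The downside is that (a) is diluted by crossover, so neither estimate should be read alone.

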### Sample size calculation

#### A-priori power calculations

The primary response variable, change in MADRS-score between baseline and endpoint, will be done with the two-sample t-test at the significance level α = 0.05. The least clinical important difference between the treatment group (ECT) and the reference group (drug) to be detected was judged to be 4 in favour of ECT, and a SD = 7 for the change in MADRS is assumed. The possibility of an opposite effect could not be ignored and a two-sided test will be done. Thus the competing hypotheses are:

H0: Mean change in MADRS is the same in both groups vs.

HA: Mean change in MADRS is different in the two groups.

To detect a difference of 4 in mean change in MADRS between the two groups with a power of Π = 0.90 a total of n = 132 patients will have to be included in the analysis. Standard deviations of S= 6-7 are typical for MADRS in studies of patients with BD. The standard deviation for change in score is S√[2(1-R)] where R is the correlation between the two timepoints. Thus, with a correlation of at least 0.5 the standard deviation for the change will be at most S and the power at least 0.90.

Concerning changes in inflammation measures, effects sizes of more than 20-50% are expected, but standard deviations in this population will vary for different cytokines, and a formal power analysis has not been performed.

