### Description of treatment

#### Method of assigning patients to treatment groups/Randomization

Patients' eligibility will be established before randomization to one of the treatment options. Relevant patients with BD are addressed in order to establish whether they are willing to be screened for the study. The patients must be assigned a patient number and sign the consent form after receiving oral and written information about the study prior to undergoing any study procedures. Patients will be randomized strictly sequentially, as patients are eligible for randomization. If a patient discontinues from the study, the patient number will not be reused, and the patient will not be allowed to re-enter the study.

We perform a stratified randomization separately for each centre using the default random number generator of SPSS 15 with a random seed. The randomization lists are kept concealed from the investigators.

After randomization patients will enter a wash out phase if necessary. The recommended time for patients to be without concomitant medication in contradiction to the study protocol is 5 t 1/2 for patients randomized to ECT and a varying time for patients randomized to treatment as usual.

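### The unadjusted t-test on MADRS change is valid, but it is less efficient than adjusting for baseline and centre, and its 90% power needs an unsourced correlation (0.5 at S = 7, about 0.32 at S = 6)

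*Protocol article*

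**What the plan says.** The section on a-priori power calculations names the primary test: "The primary response variable, change in MADRS-score between baseline and endpoint, will be done with the two-sample t-test at the significance level" 0.05. It is two-sided ("The possibility of an opposite effect could not be ignored and a two-sided test will be done"). The difference of interest "to be detected was judged to be 4 in favour of ECT", the SD of change is assumed to be 7, and "with a power of Π = 0.90 a total of n = 132 patients will have to be included in the analysis".

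The same section supports the SD of 7 indirectly. It gives S = 6 to 7 as typical for a single MADRS score, writes the SD of change as S√[2(1−R)], and concludes that "with a correlation of at least 0.5 the standard deviation for the change will be at most S and the power at least 0.90". It cites no data or source for R.

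On allocation, the randomisation section says: "We perform a stratified randomization separately for each centre". The statistical analysis section takes visit 2, the start of treatment, as baseline. It mentions multiple regression for secondary outcomes and cognition only. For the binary outcomes, "Response and remission rates will be compared using Chi Square tests". Neither baseline MADRS nor centre appears as a covariate for the primary comparison.

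**The concern.** The article states a specific primary test and builds its power claim on it, so this is a choice made and not a detail left to an analysis plan. Two things follow.

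- **Power rests on R.** The variance of a change score grows quickly as R falls, so the 0.90 is only as good as the assumed correlation. Entry requires MADRS of at least 25 (Table 1). That restricts the spread at baseline and tends to lower R, so 0.5 cannot be taken as a safe default without evidence.
- **Baseline is used with a fixed slope.** Subtracting baseline corrects a chance imbalance with a slope of exactly 1. If the SDs at the two visits are equal, as the article's formula assumes, the regression slope is R. At R = 0.3, a 1-point chance imbalance at baseline carries 0.3 points into the endpoint, but the change score removes 1 point. The estimate then shifts by 0.7 points in the other direction. A fitted slope avoids this.

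At stake is precision that the trial could have from data it already collects, and a power statement that a reader cannot verify.

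**Working it through.** **Inputs.** From the power section: difference 4, two-sided α = 0.05, SD of change 7, S = 6 to 7, N = 132, and the formula for the SD of change. From the abstract and the subjects section: nine centres. Assumed: 1:1 allocation (66 per arm), because the ratio is not stated.

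**Step 1: the plan's own figure.** The standard error is 7 × √(2/66) = 1.219, so the noncentrality is 4/1.219 = 3.28 on 130 df. The exact noncentral-t power is 0.903, and 66 per arm is the smallest size that reaches 0.90. The normal approximation gives 65 per arm. N = 132 is reproduced.

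**Step 2: the correlation this needs.** S√[2(1−R)] ≤ 7 means R ≥ 1 − 49/(2S²):
- S = 7: R ≥ 0.50
- S = 6.5: R ≥ 0.42
- S = 6: R ≥ 0.32

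**Step 3: t-test against ANCOVA at S = 7.** The residual SD after adjusting for baseline is S√(1−R²). The ratio of the two variances is 2(1−R)/(1−R²) = 2/(1+R), which exceeds 1 for any R below 1. ANCOVA has 129 df, or 121 with eight centre indicators.

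| R | SD of change | t-test power, N = 132 | N for 0.90 | ANCOVA SD | ANCOVA power, N = 132 | N for 0.90 |
|---|---|---|---|---|---|---|
| 0.5 | 7.00 | 0.903 | 132 | 6.06 | 0.964 | 100 |
| 0.4 | 7.67 | 0.845 | 158 | 6.42 | 0.945 | 112 |
| 0.3 | 8.28 | 0.786 | 184 | 6.68 | 0.927 | 120 |
| 0.2 | 8.85 | 0.731 | 208 | 6.86 | 0.914 | 126 |
| 0 | 9.90 | 0.635 | 260 | 7.00 | 0.903 | 132 |

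The ANCOVA columns adjust for baseline only. Adding the eight centre indicators changes power by no more than 0.001. Any gain from centre itself is not counted, because no between-centre variance is given.

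**Step 4: the lower end of the range, S = 6.** t-test power is 0.967, 0.895 and 0.852 at R = 0.5, 0.3 and 0.2. ANCOVA power is at least 0.967 for every R from 0 up.

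**Step 5: relaxing the common SD.** The formula assumes the same S at both visits. If the SDs differ, the SD of change is √(s_b² + s_e² − 2R·s_b·s_e) and the ANCOVA SD is s_e√(1−R²), where s_b is the baseline SD and s_e the endpoint SD. The SDs below are assumptions. R runs from 0.1 to 0.5.

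| Baseline SD | Endpoint SD | t-test power | ANCOVA power |
|---|---|---|---|
| 5 | 7 | 0.80–0.96 | 0.91–0.96 |
| 5 | 9 | 0.64–0.83 | 0.72–0.83 |
| 7 | 9 | 0.56–0.80 | 0.72–0.83 |

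ANCOVA is never lower in these cases, but it does not secure 0.90 once the endpoint SD exceeds 7 by much. The two methods converge when R·s_e/s_b is near 1. With SDs 5 and 9 and R = 0.5, that ratio is 0.9 and the powers are 0.832 and 0.833.

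**The case against.** The strongest defence is that nothing here is invalid. Under randomisation, a t-test on change gives an unbiased comparison. The sample size reproduces exactly. The article shows its formula and states the condition on R openly. R = 0.5 is needed only at S = 7, the top of the range given. All of this stands, and it limits the point to efficiency and to an unsourced assumption.

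Three stronger readings are tempting, and the document does not support them.

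- *Ignoring the stratification factor makes the standard error too large and the test conservative.* That requires allocation to be balanced within centre and outcomes to differ between centres. The randomisation section describes a random number generator used separately per centre. It mentions no blocks, and no between-centre variance is given. Under simple randomisation within centre, the unadjusted test keeps its nominal size.
- *Chance baseline imbalance goes uncorrected.* It does not. The change score corrects it, but with a fixed slope of 1.
- *ANCOVA guarantees 0.90 whatever R is.* This holds only if the endpoint SD is at most 7. Entry at MADRS 25 or above may narrow the baseline spread, and mixed response may widen the spread at endpoint. Dropping the condition on R without putting one on the endpoint SD would replace one unsupported assumption with another.

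Replacing the chi-square tests for response and remission is also a matter of preference. They are valid for secondary outcomes.

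**Conclusion.** The point holds as a low-cost improvement, not as an error in the test or the sample size. On the article's own inputs at S = 7, the planned test falls from 0.90 power at R = 0.5 to 0.79 at R = 0.3 and 0.73 at R = 0.2. Baseline-adjusted analysis stays between 0.91 and 0.96 over the same range. Even if R = 0.5 is right, adjustment cuts the chance of missing a true 4-point difference from about 10% to about 4%. If S is nearer 6 the t-test is less exposed, with 0.90 reached at R of about 0.32.

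These figures assume 1:1 allocation, 132 patients analysed and, for the main table, one common SD at both visits. No numerical claim is made for the centre term. It belongs in the model because randomisation is stratified on it, and its cost in degrees of freedom is negligible.

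**What to change.** 1. **Primary analysis.** Specify a linear model of week-6 MADRS (or change) on arm, baseline MADRS and centre, with small centres pooled by a stated rule. Report the adjusted difference with its 95% confidence interval. Keep the t-test on change as a sensitivity analysis.
2. **Which baseline.** State which visit supplies the covariate. Baseline is now visit 2, but washout follows randomisation and its recommended length is set differently for the two arms, so the visit-2 score may already reflect the assigned arm. The change score has the same exposure. MADRS is also taken at visit 1 (Table 4). Modelling week-6 score or change gives the same treatment estimate only if the covariate is the baseline from which the change is taken.
3. **Power statement.** Give a source for R, or drop the reliance on it. State power as at least 0.90 under ANCOVA on condition that the endpoint SD is at most 7. Tabulate it over R and endpoint SD, including less favourable cases such as 0.72 to 0.83 at an assumed endpoint SD of 9 and R from 0.1 to 0.5.
4. **Optional.** For response and remission, a centre-stratified test or a logistic model with the same terms would match the primary model.

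The cost is a change of wording and about nine degrees of freedom (one for baseline, eight for centre). It needs no extra patients, visits or measurements.

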### Subjects

#### Trial sample and recruiting centres

132 patients fulfilling the criteria below will be included into this study by nine centres in Norway.

All the patients will first be included in the "Bipolar Research And Innovation Network, Norway" (BRAIN) study, a multicenter study describing bipolar disorder patients in Norway. This study is approved by The Regional Committee for Medical and Health Research Ethics, Middle - Norway. The patients will give written informed consent both to the BRAIN study and the ECT-study.

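### The 132 patients needed in the analysis for 0.90 power are also the number enrolled, so the stated power holds only if at most one patient is lost from the efficacy set

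*Protocol article*

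**What the plan says.** Under A-priori power calculations, the comparison of MADRS change "will be done with the two-sample t-test at the significance level α = 0.05". The test is two-sided. The difference to detect "was judged to be 4 in favour of ECT", and "a SD = 7 for the change in MADRS is assumed". For power 0.90 the section concludes that "a total of n = 132 patients will have to be included in the analysis". That is a count of patients analysed.

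Under Trial sample and recruiting centres, "132 patients fulfilling the criteria below will be included into this study by nine centres in Norway". The abstract gives the same figure as the sample. Neither place adds a margin.

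The Statistical analysis section limits the efficacy analyses to those who receive "at least one medication with study medicine and provide post - baseline efficacy measurements will be included in efficacy data analyses (intention to treat"). It carries the last observation forward for patients who leave early.

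The randomisation section places any wash-out after randomisation and before treatment. It also says that the number of a patient who discontinues is not used again and that the patient may not re-enter. The Study design section adds that "the patient may leave the study at all times".

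**The concern.** One number serves two purposes. The power section treats 132 as what the analysis needs, and the recruitment section treats it as what the trial will enrol. Both can be true only if every randomised patient reaches the efficacy set. The plan's own definition of that set does not guarantee this: a patient who leaves during wash-out has received no study treatment, and one who leaves before any rating on treatment has no post-baseline value. Neither can be recovered by carrying an observation forward.

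At stake is the power claimed for the main question. If it is overstated, a non-significant result will be read as somewhat stronger evidence against a 4-point difference than it is. Four points is what the protocol itself treats as the smallest difference of clinical importance.

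**Working it through.** **Inputs, all from A-priori power calculations unless noted**
- Difference in mean change, δ = 4.
- SD of change, σ = 7.
- α = 0.05, two-sided: "The possibility of an opposite effect could not be ignored and a two-sided test will be done".
- Target power 0.90.
- Allocation 1:1. This is assumed; the document names two groups but gives no ratio.
- Loss rate: none is given, so every rate below is an assumption.

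**Step 1: reproduce the plan's figure**

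Normal approximation: n per arm = 2(σ/δ)²(1.960 + 1.282)² = 2 × 3.0625 × 10.51 ≈ 64.4. This rounds up to 65 per arm, or 130 in total.

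Exact two-sample t-test: the noncentrality parameter is δ / [σ√(1/n₁ + 1/n₂)], on n₁ + n₂ − 2 degrees of freedom. With 66 per arm it is 4 / [7√(2/66)] = 3.283, the critical value is 1.978, and power is 0.903. With 65 per arm power is 0.8985. So 132 is the smallest equal-arm total that reaches 0.90, and the stated figure is reproduced.

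**Step 2: the reserve**

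| Analysed | Arms | Power (σ = 7) |
|---|---|---|
| 132 | 66 + 66 | 0.903 |
| 131 | 66 + 65 | 0.901 |
| 130 | 65 + 65 | 0.8985 |

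One lost patient is absorbed. The second takes power just below 0.90.

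**Step 3: assumed losses from the efficacy set**

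The analysed number is 132 × (1 − d), with noncentral t power at that number.

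| Assumed loss d | Analysed | Power, σ = 7 | Power, σ = 6 |
|---|---|---|---|
| 0% | 132 | 0.903 | 0.967 |
| 2% | 129.4 | 0.897 | 0.964 |
| 5% | 125.4 | 0.888 | 0.959 |
| 10% | 118.8 | 0.870 | 0.950 |

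In whole patients, 125 (63 + 62) gives 0.887 and 119 (60 + 59) gives 0.871.

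**Step 4: who can be lost under the written rules**

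- Lost: patients never treated after randomisation, and patients treated but with no post-baseline efficacy rating.
- Kept: patients who leave later with at least one rating. Table 4 schedules MADRS weekly from week 1, and the last value is carried forward.

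The loss that matters is therefore loss before the first rating on treatment. Loss before week 6 is a different and larger quantity.

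**The case against.** The strongest reply is that few patients can leave the efficacy set. MADRS is rated every week from week 1, patients must be inpatients for the first treatment week, anyone who discontinues must be seen for a final evaluation, and the last observation is carried forward. Nothing says that anyone will be excluded. This stands, and it is why the small loss rates are the relevant ones. It does not remove the point, because wash-out falls between randomisation and treatment and none of these safeguards reaches a patient who leaves then.

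A second reply is that SD 7 is the top of the 6–7 range given for MADRS, so the calculation has slack. At an SD of change of 6, power stays at 0.95 even after 10% loss. This is true but conditional. The section equates the SD of change with the SD of a single score only when the correlation between time points is at least 0.5. That correlation is assumed, not shown. With S = 7 and R = 0.3, the section's own formula gives 7 × √1.4 = 8.28, and power with all 132 analysed is 0.79. The SD is not a dependable reserve.

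A reader might also infer more than the document supports:
- *Any loss breaks the claim.* It does not: 131 analysed still gives 0.901.
- *Losses of 20–30% apply, because patients without a week-6 score drop out of the analysis.* That describes an analysis of completers. The article plans one as an addition, but the main efficacy analysis carries observations forward.
- *Early leavers are lost because taping is scheduled only at visits 2 and 8.* No passage excludes a patient who has only investigator ratings. How taped scores combine with carried-forward values is a separate question.

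**Conclusion.** The point holds in a limited form. The sample size arithmetic is correct. What is wrong is using the required analysed number as the enrolment number while the plan's own efficacy set can be smaller than the number randomised, with no allowance or replacement stated. Under the protocol's own assumptions the design delivers 0.90 only if at most one patient is lost from that set.

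The size is probably modest: about 1.5 points of power at an assumed 5% loss (0.903 to 0.888) and about 3 points at 10% (0.903 to 0.870). These figures rest on a difference of 4, an SD of change of 7, 1:1 allocation, an unadjusted t-test and loss rates that the document does not supply. If the SD of change were 6, power would remain above 0.90 throughout this range. It would go too far to conclude that the trial is seriously underpowered. The document supports only that the quoted power is somewhat too favourable for the design as written.

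**What to change.** Keep 132 and describe it in every place as the number randomised, not the number analysed. In A-priori power calculations, state the loss expected from the efficacy set as the article defines it (never treated, or no post-baseline rating), and restate power at the resulting number. For example, with a difference of 4 and an SD of 7, power is about 0.89 with 125 analysed and about 0.87 with 119. The sponsor should supply the expected loss rate, since none is given.

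The cost is one or two sentences and a slightly less favourable power figure. Recruitment, conduct and the planned test do not change.
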